## Abstract

**Background:**

The risk of cardiovascular diseases (CVDs) is becoming more prevalent in pregnant women though not much data is available for pregnant women with human immunodeficiency virus (HIV). Foetoplacental vascular endothelial dysfunction is thought to be at the origin of chronic diseases such as diabetes and obesity later on in life. Because HIV and anti-retroviral treatment (ARTs) are associated with endothelial dysfunction, children exposed in utero to these conditions may be at greater risk of developing CVDs. Despite the high prevalence of HIV in pregnant South African women, little is known about the effects of ART on the cardiovascular health of the mother and offspring. Hence, the proposed study intends to investigate how HIV/ARTs may affect the cardiovascular health of the mother and offspring at different time points during the pregnancy and up to 2 years after birth.

**Methods:**

A longitudinal case–control study in HIV positive pregnant women on ART and HIV negative pregnant women will be conducted. All pregnant women will be assessed for cardio-metabolic risk factors and markers (lipids, anthropometric and glycaemic indies, oxidative stress), hemodynamic status (blood pressure parameters) and vascular function (arterial compliance, retinal microvasculature, uterine artery mean pulsatility index). Child health will be monitored in utero and postnatally via routine foetal health screening, placental integrity, anthropometry, blood pressure parameters, markers of oxidative stress and endothelial function in cord blood and cardiovascular epigenetic markers in urine.

**Discussion:**

There is a paucity of studies in South Africa and sub-Sahara Africa as a whole that utilised a longitudinal study model to assess the effects of ARTs on vascular endothelial changes in pregnant women living with HIV and the cardiometabolic health of their offspring. This study will therefore help to monitor changes in cardiometabolic risk during pregnancy and in children exposed in utero to HIV-infection and ART use. Findings from this study will provide useful information for developing guidelines on the use of ARTs in pregnancy and management of cardiometabolic health of the offspring of HIV positive mothers.

**Supplementary Information:**

The online version contains supplementary material available at 10.1186/s12872-021-02130-2.

## Background

According to the World Health Organisation (WHO), approximately 17.9 million deaths were recorded due to cardiovascular diseases (CVDs) globally in 2016 which translates to about 31% of all-cause mortality [1]. It should be noted that 75% of these deaths occurred in low and middle income countries [1]. Risk factors for the development of CVDs include obesity, hypertension, dyslipidaemia, endothelial dysfunction, inflammation, microalbuminuria, insulin resistance, oxidative stress, etc. [2]. The prevalence of some of these risk factors is very high in the general South African population: obesity (20–25%), hypertension (10.2%), dyslipidemia (24%) and insulin resistance (10–20.7%) [3] thus explaining why CVDs may contribute significantly to death rates in South Africa [4]. Vascular abnormalities such as arteriolar-venular nicking and increased carotid intima–media thickness, and focal and generalized arteriolar narrowing in adults have been associated with CVDs [5, 6]. Changes in arterial structure generally take a long time to be discernible in the larger vessels. Detectable changes however are more readily noticeable in the smaller vessels thus presenting an opportunity for early assessments. These microcircular changes can be non-invasively assessed and monitored in the retina using fundoscopy [7–10]. Whereas widening of retinal venules is linked to endothelial dysfunction and inflammation, narrowing of retinal arterioles is linked to increased blood pressure and endothelial dysfunction. Both of these changes in the retinal microvascular are indicative of endothelial dysfunction, a major cardiovascular risk factor.

Recent reports show that people living with HIV (PLWH) have an abundance of traditional CVD risk factors and may therefore be at increased risk of CVDs [11, 12]. Indeed, a prospective cohort study for a 6-year period with over 80,000 HIV-infected persons showed that HIV-infected adults with hypertension had a twofold higher risk of developing acute myocardial infarction than uninfected adults with hypertension [13]. Also, studies have shown obesity and dyslipidaemia to be prevalent in HIV patients [14]. In South Africa, the prevalence of CVD risk factors in HIV continues to rise creating a major public health concern for the country [15, 16]. HIV/AIDS seems to be on a collision course with a rapidly increasing burden of cardiovascular risk factors and disease in this population [17–19]. Indeed it is projected that by 2030, about 84% of HIV-infected patients will be affected by at least one non-communicable disease with over one-third of HIV patients having three or more non-communicable diseases [20].

While PLWH now live longer, thanks to the availability of anti-retroviral treatments (ARTs) though there are concerns that some ARTs may be associated with dyslipidaemia, hypertension and dysglycaemia [21]. Studies have shown that ARTs are associated with dysregulation of plasma lipid levels and metabolism [22–24]. Also, ARTs may affect glucose homeostasis and promote insulin resistance [21]. Furthermore, HIV-infected adults on ART have a higher prevalence of hypertension when compared with HIV-uninfected individuals [25]. These findings seem to suggest that ARTs may improve the life expectancy of PLHW but also make them more vulnerable to developing CVDs on the long run. Also, ART may cause direct endothelial injury and promote endothelial dysfunction [26], which is an important risk factor for CVDs. Although ART and HIV have been associated with CVDs, such findings are yet to be established in HIV pregnant women [27, 28].

Globally, over 1.4 million pregnant women are living with HIV [29]. Among this population, about 960,000 HIV-infected pregnant women reside in Eastern and Southern Africa. In South Africa, 30.2% of all pregnant women who attended public health-care facilities in 2012 were infected with HIV [30]. The risk of CVD is becoming more prevalent in pregnant women [31] though not much attention has been paid to this population. Gestational diabetes mellitus (GDM) is associated with macro and microvascular endothelial dysfunction of the placenta mainly triggered by hyperinsulinemia, hyperglycaemia, and changes in nucleoside extracellular concentration [32].

Endothelial dysfunction may alter the intrauterine environment of the foetus. Foeto-placental vascular endothelial dysfunction may cause epigenetic alteration in the intrauterine environment of the foetus. This may be the origin of chronic diseases such as diabetes and obesity in childhood predisposing children to CVDs which may track into adulthood [33]. According to the concept of the Developmental Origins of Health and Disease, the maternal environment/gestational milieu may have a significant impact on the health of the offspring in adulthood and may be responsible for programming children for CVDs later on in life [34]. Indeed, poor placental perfusion as in pre-eclampsia has been associated with preprograming for obesity, hypertension and diabetes in adult life [35]. Animal studies have shown that administration of combination ART during pregnancy was associated with poor placental insertion and development resulting in growth restricted offspring [36]. Because HIV infection and ARTs are associated with increased cardiovascular risk factors including endothelial dysfunction, we hypothesize that HIV-infection/ARTs will promote endothelial dysfunction which will engender poor placental perfusion resulting in offspring being pre-programed for increased cardiovascular risk later on in life.

Though PLWH now enjoy a longer lifespan following the introduction and ready availability of ARTs, the long-term safety of ART use among pregnant women is not known [37], much less its impact on the foetus, neonates and children born after in utero exposure to these drugs. There is currently no information on epigenetic changes if  in children exposed to HIV infection/ART environment or how these changes may relate to preprograming for increased susceptibility to cardiometabolic conditions later on in life. Furthermore, there is not yet a scientific explanation for the high prevalence of CVDs in young Africans and their high vulnerability to target organ damage at earlier age compared to other races [38]. South Africa has the highest prevalence (13.0%) of HIV infection globally and at least 68% of all patients diagnosed with HIV are on ARTs [39] thus making South Africa the ideal setting for determining the cardiometabolic effects of HIV/ART use on mother and offspring.

## Methods/design

### Aim and objectives

The aim of this study is to investigate whether HIV-infection and ART are associated with risk of cardiometabolic diseases in pregnant women of African ancestry and their offspring after birth. This study aims to:Assess cardiometabolic disease risk in HIV positive pregnant women on ART and HIV negative pregnant women.Determine foetal health in the maternal HIV/ART environment during the three trimesters of gestation.Assess cardiometabolic health of mothers exposed to HIV/ART at various time points after delivery.Assess cardiometabolic risk in offspring of HIV positive mothers who were on ART during pregnancy at birth at predetermined time points after birth.

### Ethical approval

Ethical consent and permission to carry out the research project was obtained from the Faculty of Health Sciences Research and Ethics Committee (HRSEC No: 017/2020) at Walter Sisulu University (WSU). The study was approved by the Eastern Cape Provincial Department of Health, South Africa and then registered with the NIH (Protocol ClinicalTrials.gov Identifier: NCT04763668; https://clinicaltrials.gov/ct2/show/NCT04763668). The purpose of the study will be explained to women attending the antenatal clinic in the Mthatha Regional and Nelson Mandela Academic Hospitals, Mthatha, Eastern Cape Province. Pregnant women who will be willing to participate will be required to sign informed consent forms to participate in the study and to allow their children to participate in the study from birth.

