### Selection criteria

Pregnant women of African ancestry with singleton uncomplicated 11–14 week old pregnancies, who are either HIV positive for the case group or HIV negative for the control group will be recruited for the study. Pregnant women with type 2 diabetes, gestational diabetes, renal and CVDs or any critical health condition will be excluded from the study. Furthermore, data will not be collected from eligible pregnant women who have eaten, smoked or done physical exercise 6 h prior to data collection.

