### Study design and experimental plan

A prospective case–control design will be employed for this study. This will include HIV positive pregnant women on ART and HIV negative pregnant women who will serve as control. HIV positive pregnant women below 35 years of age with singleton pregnancy on ART attending antenatal clinic at  Mthatha Regional  Hospital and Nelson Mandela Academic Hospital, Mthatha will be recruited for the study and followed up during pregnancy for the presence of cardiovascular risk factors. In addition, foetal health and cardiometabolic health of the babies born to recruited women will be assessed after birth and up to 24 months after birth.

Recruited, pregnant women with known HIV positive status and who have been on ART for over 4 months will be counselled and screened for HIV to confirm their status. Thereafter, pregnant women will be assessed during antenatal visits in the first trimester (11–14 weeks), second trimester (24–26 weeks) and third trimester (35–37 weeks) for cardiometabolic risk factors including obesity, hypertension, albuminuria, insulin resistance, dyslipidaemia, oxidative stress and endothelial dysfunction. The viral load and CD4 count will be determined in the mothers at baseline and third trimester of pregnancy. A structured interviewer administered questionnaire will be used to collect data on their baseline characteristics including demographic, obstetric and family history of CVDs while anthropometric and blood pressure measurements will be performed. Placental morphometry will be assessed by ultrasound while vascular health will be assessed via pulse wave velocity (Vicorder, SMT GmbH, Germany) and endothelial function markers in blood. Microvasculature assessment will be done via retinal imaging using a retinal camera (Optomed, Finland) as previously reported [40]. Blood samples will be collected for the assessment of endothelial function markers [41], oxidative stress, lipid profile and insulin resistance markers [42] while urine will be collected for assessment of renal function. Mothers will have one post delivery follow-up for CVD risk assessment.

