#### Statistical analysis

Data analyses will be carried out using IBM statistical package for social sciences (SPSS) Version 23.0 (IBM Corp.). Armonk, NY, USA) and STATA. Data will be checked for normality using Shapiro-Wilks test and log-transformed and/or corrected for outliers when necessary. Descriptive statistics are presented as mean ± standard deviation (SD). Mean differences between groups (HIV positive pregnant women and HIV negative pregnant women) will be done using independent sample t-test. Analysis of variances (ANOVA) will be used to compare continuous variables between three or more groups. Multivariate analysis using multiple analysis of variance (MANOVA) will be used to compare continues variables for two or more independent variables (ART, HIV etc.). Chi-square test will be used to associate cardiovascular risk factors at baseline and follow-up for both mother and child. Pearson correlation will be used to assess relationship between risk factors of CVD. Linear and binomial logistic regressions will be employed to assess the risk of CVDs due to HIV and ART. A confidence interval of 95% will be taken and α = 0.05 will be considered for level of significance.

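### The 80:80 recruitment is not tied to hospital and the group means are compared by an unadjusted t-test, so any hospital imbalance would enter the HIV/ART contrast; a hospital-adjusted regression is a cheap improvement

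*Protocol article*

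**What the plan says.** **Where the women come from.** The section on ethical approval describes one pool to be approached: "women attending the antenatal clinic in the Mthatha Regional and Nelson Mandela Academic Hospitals". The selection criteria apply to women "who are either HIV positive for the case group or HIV negative for the control group will be recruited for the study" and mention no hospital. The study design section names the two hospitals again in a sentence about cases, "HIV positive pregnant women below 35 years of age with singleton pregnancy on ART". Of the other group it says only "HIV negative pregnant women who will serve as control".

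**How many.** The sample size section fixes 80 cases and 80 controls in total. It gives no number or ratio per hospital, and no other section mentions matching, quotas or stratified recruitment by hospital.

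**How they are compared.** The statistical analysis section states: "Mean differences between groups (HIV positive pregnant women and HIV negative pregnant women) will be done using independent sample t-test". It also plans ANOVA, MANOVA with HIV and ART among the factors, and regression: "Linear and binomial logistic regressions will be employed to assess the risk of CVDs due to HIV and ART". No covariates are listed for these models, and hospital is not mentioned. The baseline questionnaire includes the participant's location, but recruiting hospital is not named as an item.

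**The concern.** The groups are formed by HIV status, not by randomisation, so nothing in the design balances hospital between them. Even when both groups attend the same two clinics, each group can fill at a different rate in each, and the mixes can then differ. The method stated for the group means takes no account of this. A hospital difference in case mix or measurement would then appear as part of the HIV/ART effect.

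Some outcomes depend on the operator. Pulse wave velocity relies on carotid palpation, cuff placement and a tape-measured path length, and several placental indices come from ultrasound. A hospital difference is therefore conceivable, though the article does not show one. The article expects its findings to inform guidance on ART in pregnancy, so an artefact of this kind would matter if it occurred.

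**Working it through.** **1. The plan's own figure.** With d = 0.5, two-sided α = 0.05 and power 0.80, the noncentral-t solution is 63.77, so 64 per group, as stated. Then 64 × 1.25 = 80, as stated. The hospital question does not depend on this figure; it only supplies the group size.

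**2. Inputs.** From the article: 80 per group, α = 0.05, planned d = 0.5. Assumed, because the article gives neither: a hospital difference D in the outcome, in within-hospital SD units, and the shares p₁ (cases) and p₀ (controls) from one of the two hospitals.

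**3. Formulas, with no true HIV/ART effect.**
- Bias = D × (p₁ − p₀).
- Total variance within a group = 1 + D² × [p₁(1 − p₁) + p₀(1 − p₀)]/2.
- Noncentrality = (bias/√variance) × √(n/2). The false-positive rate is the two-sided tail of the noncentral t with 2n − 2 degrees of freedom.

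Worked case, D = 0.5 and 60/40 versus 40/60: bias = 0.5 × 0.2 = 0.10; variance = 1 + 0.25 × 0.24 = 1.06; noncentrality = (0.10/1.030) × √40 = 0.61; false-positive rate 9.4%.

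**4. Results at 80 per group (bias in SD; type I error of the t-test).**

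| D | Equal mix | 60/40 vs 40/60 | 70/30 vs 30/70 |
|---|---|---|---|
| 0.2 | 0; at most 5% | 0.04; 5.7% | 0.08; 7.9% |
| 0.3 | 0; at most 5% | 0.06; 6.6% | 0.12; 11.6% |
| 0.5 | 0; at most 5% | 0.10; 9.4% | 0.20; 23.2% |
| 0.8 | 0; at most 5% | 0.16; 15.5% | 0.32; 47.2% |

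If a quarter of the women are lost (80 × 0.75 = 60 per group), the 0.3 to 0.5 SD range gives 6.2 to 8.2% at 60/40 and 9.9 to 18.5% at 70/30. The rates treat hospital as sampled with the given probabilities; with the shares held exactly fixed they would be slightly lower.

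**5. Cost of adjusting.** The squared correlation between group and hospital is [(p₁ − p₀)²/4]/0.25 when hospital is split evenly overall. At 60/40 it is 0.01/0.25 = 0.04, so the variance inflation is 1/0.96 = 1.04. At 70/30 it is 0.16, giving 1/0.84 = 1.19. In evaluable women per group, 64/0.96 = 66.7, so 67; 64/0.84 = 76.2, so 77. At 80/20 it would be 64/0.64 = 100. If all cases came from one hospital and all controls from the other, hospital and exposure could not be separated.

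**6. If the mix is equal.** Leaving hospital out adds D²/4 to the variance: 0.0225 to 0.0625 for D = 0.3 to 0.5, about 2 to 6%. That is minor.

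**The case against.** The case against is substantial, and most of it stands.

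- *The t-test is not the only analysis.* A reader might infer that the whole trial rests on one unadjusted comparison. It does not: MANOVA and regressions for HIV and ART are planned, and the t-test is not labelled primary. Their covariates are unlisted, which a condensed article may leave to the full protocol or analysis plan, so the absence of a list is not the point. What remains is that the method actually named for the difference in means is one that cannot adjust.
- *The controls are not from elsewhere.* Because the design section names the hospitals only for HIV-positive women, a reader might infer a separate source for controls. The sections on ethical approval and selection criteria, read together, point to the same two clinics for both groups. Only the split is left open.
- *No hospital difference is shown.* A reader might take differences in operators, equipment or case mix as likely. Nothing in the article says that measurements are made separately at each hospital or by different teams. It names one device per main measure, gives a detailed pulse wave velocity procedure, uses a single masked retinal grader and applies common eligibility criteria. A difference is possible, not established.
- *The size is assumed.* This is correct. Both D and the imbalance are assumptions, and the larger rates need a split that nothing in the article suggests.

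**Conclusion.** The point holds as a modest improvement, not as an error in the plan. Followed to the letter, the plan recruits at two hospitals without tying the 80:80 allocation to hospital and compares the group means with a test that leaves any hospital imbalance in a non-randomised contrast.

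The consequence depends on two assumptions, and the bias is zero if either fails. Under a hospital difference of 0.3 to 0.5 SD and the milder imbalance, it is 0.06 to 0.10 SD, or 12 to 20% of the planned d of 0.5 (0.06/0.5 and 0.10/0.5), with a type I error of about 6.6 to 9.4% at 80 per group. The 0.20 SD and 23% at 70/30 illustrate a worse case, not an expectation. Hospital is one possible confounder here, and the article does not show that it is the one that matters most. Low priority.

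**What to change.** 1. In the data collection section, add the recruiting hospital as a recorded item.
2. In the statistical analysis section, make the linear regression already planned the main comparison of HIV-positive with HIV-negative women for continuous outcomes, with hospital as a fixed factor, in place of the t-test. Report the hospital-adjusted difference with its 95% confidence interval.
3. In the study design section, state that HIV-negative women are recruited in the same proportion as HIV-positive women within each hospital and over the same calendar period, where feasible. This belongs before enrolment, because adjustment becomes expensive once the mixes are far apart.

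The cost is one model term (about 4% in variance at a 60/40 imbalance), some bookkeeping in the recruitment log, and possibly slower control recruitment at one hospital. No extra measurements are needed, and if recruitment is kept proportional the target of 64 evaluable women per group is unchanged.

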### Selection criteria

Pregnant women of African ancestry with singleton uncomplicated 11–14 week old pregnancies, who are either HIV positive for the case group or HIV negative for the control group will be recruited for the study. Pregnant women with type 2 diabetes, gestational diabetes, renal and CVDs or any critical health condition will be excluded from the study. Furthermore, data will not be collected from eligible pregnant women who have eaten, smoked or done physical exercise 6 h prior to data collection.

### Study design and experimental plan

A prospective case–control design will be employed for this study. This will include HIV positive pregnant women on ART and HIV negative pregnant women who will serve as control. HIV positive pregnant women below 35 years of age with singleton pregnancy on ART attending antenatal clinic at  Mthatha Regional  Hospital and Nelson Mandela Academic Hospital, Mthatha will be recruited for the study and followed up during pregnancy for the presence of cardiovascular risk factors. In addition, foetal health and cardiometabolic health of the babies born to recruited women will be assessed after birth and up to 24 months after birth.

Recruited, pregnant women with known HIV positive status and who have been on ART for over 4 months will be counselled and screened for HIV to confirm their status. Thereafter, pregnant women will be assessed during antenatal visits in the first trimester (11–14 weeks), second trimester (24–26 weeks) and third trimester (35–37 weeks) for cardiometabolic risk factors including obesity, hypertension, albuminuria, insulin resistance, dyslipidaemia, oxidative stress and endothelial dysfunction. The viral load and CD4 count will be determined in the mothers at baseline and third trimester of pregnancy. A structured interviewer administered questionnaire will be used to collect data on their baseline characteristics including demographic, obstetric and family history of CVDs while anthropometric and blood pressure measurements will be performed. Placental morphometry will be assessed by ultrasound while vascular health will be assessed via pulse wave velocity (Vicorder, SMT GmbH, Germany) and endothelial function markers in blood. Microvasculature assessment will be done via retinal imaging using a retinal camera (Optomed, Finland) as previously reported [40]. Blood samples will be collected for the assessment of endothelial function markers [41], oxidative stress, lipid profile and insulin resistance markers [42] while urine will be collected for assessment of renal function. Mothers will have one post delivery follow-up for CVD risk assessment.

Foetal health will be assessed ultrasonically in utero during the three trimester of pregnancy. Fetal health measurements will include biparietal diameter, head circumference, abdominal circumference, thoracic circumference, crown-rump length, crown-rump length and femur length. After delivery, In addition, at three, six, twelve and twenty-four months after birth, cardiometabolic risk factors will be assessed by determining BMI, blood pressure, albuminuria, oxidative stress, endothelial function as well as epigenetics markers in urine samples.

All pregnant participants will be required to fast overnight and will be asked to restrain from drinking coffee, smoking and doing exercise for 4–6 h before assessments. The study design along with the inclusion and exclusion criteria, and the series of assessments with the timeline are summarised in Figs. 1 and 2 respectively.

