### Data collection

A structured interviewer administered questionnaire will be used for the collection of participant’s baseline characteristics and cardiometabolic risk factors (Additional file 1 - Cardiometabolic risk questionnaire). The questionnaire will contain socio-demographic information including personal data (age, sex, location and ethnicity), socio-economic status (profession, economic status, living standard). It will also contain information on maternal obstetric history, cardiometabolic health history, family history, alcohol consumption, smoking, feeding habit and physical exercise. Data will be collected using a questionnaire only at the beginning of the study.

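### The under-35 limit is written for HIV-positive women only and the named comparison of means is unadjusted, so age and social differences could be mixed with the HIV/ART contrast

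*Protocol article*

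**What the plan says.** Four parts of the protocol article bear on this.

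- **Study design and experimental plan.** The age limit sits in the sentence on cases: "HIV positive pregnant women below 35 years of age with singleton pregnancy on ART attending antenatal clinic". The comparison group appears only as "HIV negative pregnant women who will serve as control", with no age bound.
- **Selection criteria.** One set of criteria covers women "who are either HIV positive for the case group or HIV negative for the control group will be recruited for the study". It deals with ancestry, singleton uncomplicated pregnancy, gestational age and medical exclusions. It has no age limit and no matching. The criteria are also summarised in a figure that is not shown: "The study design along with the inclusion and exclusion criteria, and the series of assessments with the timeline are summarised in Figs. 1 and 2".
- **Statistical analysis.** "Mean differences between groups (HIV positive pregnant women and HIV negative pregnant women) will be done using independent sample t-test". The same section plans MANOVA with ART and HIV as independent variables, and linear and logistic regressions for the risk due to HIV and ART. No confounder is named in any of them.
- **Data collection.** The baseline questionnaire records age and socio-economic status. "It will also contain information on maternal obstetric history, cardiometabolic health history, family history, alcohol consumption, smoking, feeding habit and physical exercise".

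**The concern.** The study is called case-control, but the groups are defined by HIV/ART exposure and followed forward. The contrast is therefore a non-randomised cohort comparison, and nothing in the design balances the groups.

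Two things follow from the text as it stands. First, a 36-year-old HIV-negative woman appears eligible and a 36-year-old HIV-positive woman does not. Second, a t-test takes the whole difference in means as the group difference, whatever part of it comes from age, parity, smoking, alcohol or living standard. Blood pressure, arterial stiffness, lipids and glycaemia can all be expected to vary with such factors. The findings are meant to inform guidance on ART in pregnancy, so a spurious difference and a hidden one would both matter.

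**Working it through.** **1. The plan's own figure.** The inputs, from the sample size section, are α = 0.05, power 0.80 and d = 0.5. For a two-sided two-sample t-test, the noncentrality is d√(n/2) on 2n − 2 degrees of freedom. With n = 64 it is 0.5 × √32 = 2.83 and power is 0.801; with n = 63 power is 0.795. The stated 64 per group is reproduced. A one-sided calculation gives 50 and does not match. The sample size therefore fits an unadjusted comparison of two means.

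**2. Bias from an age cut in cases only.** The article gives no age mean, age SD or age-outcome correlation, so all three are assumed:

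- maternal age normal with nominal mean 26 to 30 and SD 6, restricted to 18–45 years;
- cases from the same distribution, restricted to below 35;
- correlation r of age with outcome 0.2 to 0.4.

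Bias in outcome SDs = r × (age gap ÷ age SD in controls).

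| Nominal mean age | Controls aged 35+ | Age gap (years) | Age SD, controls | Bias, r = 0.2 | r = 0.3 | r = 0.4 |
|---|---|---|---|---|---|---|
| 26 | 7.3% | 0.82 | 5.09 | 0.032 | 0.048 | 0.065 |
| 27 | 9.6% | 1.05 | 5.23 | 0.040 | 0.060 | 0.080 |
| 28 | 12.6% | 1.32 | 5.35 | 0.049 | 0.074 | 0.099 |
| 30 | 20.2% | 1.99 | 5.51 | 0.072 | 0.108 | 0.145 |

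With no true effect and 64 per group, the nominal 5% error becomes 5.4% at the smallest bias and 12.8% at the largest. If the true d is 0.5 and the bias opposes it, a bias of 0.05, 0.10 or 0.15 SD leaves power of 71%, 61% or 50%. If the bias runs with the effect, the difference is exaggerated instead.

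**3. The direction is not fixed.** Step 2 assumes that both groups have the same age distribution before the cut. Suppose instead that HIV-positive women have nominal mean 30 and HIV-negative women nominal mean 26 (same SD and 18–45 range). The cut cases then average 28.24 years and the uncut controls 27.07. Controls are 28.24 − 27.07 = 1.17 years *younger*, and the sign of the bias reverses.

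**4. Age gaps from unmatched recruitment in general.** A total gap of 3 years from any cause, with an assumed age SD of 6, gives a bias of r × 3/6, that is 0.10, 0.15 or 0.20 SD for r = 0.2, 0.3 or 0.4. The false-positive rate is then 8.7%, 13.4% or 20.2%. Bias from social and lifestyle differences cannot be computed from the article.

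**5. Cost of adjustment.** Approximate n per group = 64 × (1 − r²) × VIF. For an assumed remaining age gap of 0.5 SD, VIF = 1 + 0.5²/4 = 1.0625. Rounded up, n is 68, 66, 62 and 58 for r = 0.1, 0.2, 0.3 and 0.4.

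**The case against.** The best defence has four parts.

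- **The age sentence may be loose drafting.** It also ties singleton pregnancy, the two hospitals and follow-up to HIV-positive women, although the selection criteria apply singleton pregnancy to both groups and the ethics section describes recruitment at both hospitals without regard to HIV status. With Fig. 1 unseen, a common limit cannot be excluded. This stands: the asymmetry is a feature of the wording, not an established rule. The text still needs reconciling, because whoever recruits from it could apply different limits.
- **The t-test is not the only analysis.** Regressions for HIV and ART are planned, and their covariates may be listed in a document not shown. This stands in part. A missing covariate list is not the point, and nothing labels the t-test as primary. But the article does name an unadjusted test for the group means, and nothing in it gives an adjusted estimate precedence.
- **The size is assumed.** This stands. The medical exclusions may also weaken any link between age and outcome.
- **Social differences do not come from the age limit.** Correct: they arise from unmatched, non-randomised recruitment and are a separate source of confounding.

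A reader might infer that the design guarantees older controls and so hides an HIV/ART harm. The documents do not support that. It requires that controls truly have no limit and that the two groups otherwise have similar ages, and the article shows neither.

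**Conclusion.** The point holds in a limited form. In the readable text the age limit is stated for HIV-positive women only, no matching is described, and the named comparison of means in a non-randomised contrast is unadjusted. Followed as written, the plan yields a group difference that could include age, socio-economic and lifestyle differences, in either direction.

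The part due to the age cut alone is small to moderate: about 0.03 to 0.14 SD against a planning effect of 0.5 SD. It rests on assumed ages, an assumed correlation of 0.2 to 0.4, identical age distributions before the cut, and no limit for controls in Fig. 1. It shows scale and is not an estimate for this study. The remaining confounding cannot be quantified from the article. The correction is nonetheless worth making, because it is concrete and almost free.

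**What to change.** 1. **Eligibility.** Reconcile the study design section, the selection criteria and Fig. 1 so that one age criterion, whichever is intended, applies to both groups. If control recruitment has been wider, this narrows it slightly. It is best settled at recruitment: if only controls include women of 35 or over, adjustment has to extrapolate, because no cases of that age exist for comparison.
2. **Main comparison.** Make the linear regression already planned (or a mixed model for the repeated visits) the main HIV-positive versus HIV-negative comparison. Prespecify baseline covariates: age, parity or obstetric history, smoking, alcohol and socio-economic status, plus gestational age at the visit and hospital. The first five come from the baseline questionnaire; the last two should be available from the visit and site records.
3. **Secondary.** Report the unadjusted t-test beside it, so that readers can see how far adjustment moves the estimate.

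Frequency-matching controls on age band and hospital is an option, not a requirement; it would make recruitment harder. The cost is otherwise a few sentences and slightly more analysis work. By the approximation above, the adjusted comparison needs about 58 to 68 per group against the planned 64.
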